### Eligibility criteria

Potential participants must first agree to an online informed consent before beginning the baseline online survey. Inclusion criteria are being born biologically male, age 16 years or older, self-reported previous anal sex with another man, and current residence in China. Men who report past HBV vaccination, HBV testing, or HCV testing will be excluded. Those who report uncertain past HBV vaccination, HBV testing, or HCV testing will be considered eligible. All eligible participants must provide a working unique mobile phone number and WeChat account to be enrolled.

### Randomization and allocation

Once enrolled, participants will be assigned in a 1:1 ratio to intervention or control through a randomization procedure using permuted blocks. SAS software (Cary, North Carolina, USA) will be used to create the allocation sequence using the PROC PLAN and RANUNI functions. The allocation sequence will be applied to participants sequentially in the order in which they were enrolled. This RCT is not blinded. Participants will be able to determine their assignment based on whether they received intervention materials during the study period. The primary investigator (TF) will be aware of randomization assignment because intervention materials will be delivered through WeChat.

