### Study setting and recruitment

This study will be conducted online. All recruitment, enrolment, intervention delivery, and data collection will occur through mobile phones and social media smartphone apps. Nearly 70% of the adult population in China owns a smartphone, and 95% of all netizens in China access the internet using a mobile phone [27, 28]. In this study, participants will be recruited through an announcement promoted via social media accounts operated by several local MSM organizations. The announcement will include a link connecting men to the online baseline survey to be completed using a smartphone. The link will remain active until 700 eligible men have enrolled.

Once enrolled, WeChat (Tencent Holdings Limited, Shenzhen, China) will be used to deliver messages and collect confirmatory photos of hepatitis test reports from participants. Additionally, men randomly assigned to the intervention arm will view crowdsourced images and videos through WeChat. WeChat is a multipurpose social media smartphone app with messaging and multimedia functionality. The app had approximately 900 million daily active users in 2017, most of whom live in China, and is commonly used to send and share private messages, social media posts, images, and videos [29].

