### Outcomes

HBsAg and anti-HCV IgG test uptake confirmed by test report photo at 4 weeks post-enrolment is the primary outcome of this study. This dichotomous outcome has two component endpoints (HBsAg test uptake and anti-HCV IgG test uptake) that constitute a single composite endpoint. Selection of HBsAg and anti-HCV IgG as serological assays is based on WHO testing guidelines [13]. A participant will only be counted as having the primary outcome if he has submitted a photo to researchers through WeChat or the online follow-up survey that clearly displays tester age, tester sex, test date, and HBsAg and anti-HCV IgG results. If submitted HBV test report photos also include anti-HBs and anti-HBc serological assays, these results will be recorded. Test date must fall within the four-week period (28 days) after enrolment for test uptake to be confirmed.

Confirmed HBsAg and anti-HCV IgG test uptake as independent component endpoints are secondary outcomes. Secondary outcomes also include the following self-reported items on the follow-up survey: HBsAg test uptake, anti-HCV IgG test uptake, HIV test uptake, chlamydia test uptake, gonorrhoea test uptake, syphilis test uptake, visit with specialist physician after HBV or HCV testing, and change in stigma toward people living with HBV during the four-week study period. Self-reported HBV vaccination uptake among all participants and those with confirmed susceptibility to HBV infection (negative anti-HBs and negative HBsAg by test report photo) are also secondary outcomes. Definitions for all study outcomes are provided in Table 1.

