### Sample size

A pilot study was conducted in November 2017 to inform sample size calculations. Pilot results are detailed in Supplementary Materials (see Additional file 3). Assuming a confirmed HBV and HCV testing response of 8.5% among intervention participants, 3.0% among control participants, a two-sided significance level of 5%, and 10% not evaluable (e.g., missing data), a total sample size of 674 men would be needed to have 80% power for an exact test. Power was calculated in SAS version 14.2 using the *twosamplefreq* statement in PROC POWER. The total sample size was rounded up to 700 for convenience, which corresponds to approximately 82% power under the above assumptions.

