Participants will receive a WeChat message 3 weeks after enrolment asking them to complete a follow-up survey within 1 week. The follow-up survey will collect information regarding the following self-reported outcomes: HBsAg and anti-HCV IgG test uptake, consultation with a specialist physician regarding HBV and HCV test results, HBV vaccination uptake, and HIV and STI test uptake since enrolment. Stigma toward people living with HBV will be reassessed. Participants will be asked to report their exposure to intervention materials and behaviours sharing intervention materials on social media during the four-week study period. Men in the intervention and control arms will receive the same follow-up survey. Men who have not completed the follow-up survey 2 days prior to the end of the four-week study period will be sent a reminder message. Both the baseline and follow-up surveys are expected to take less than 10 min to complete and are available in Supplementary Materials (see Additional file 4 and Additional file 5).

At any time after enrolment and throughout the four-week study period participants can submit photos of their HBV and HCV test reports through WeChat. Test report photos can also be uploaded along with the follow-up survey. The following information will be extracted and recorded from submitted photos: tester age, tester sex, date of test, and test result. No other personally identifiable information will be extracted. Mobile phone numbers and WeChat accounts will be used to link information extracted from test report photos to baseline and follow-up survey responses.

Among men assigned to the intervention arm, suggestions for improving crowdsourced images and videos will be collected through a web-based survey form hosted on Wenjuanxing. Information on contest participation will be linked to baseline and follow-up survey responses using mobile phone numbers and WeChat accounts.

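### The plan does not separate acceptance of primary-outcome photos from knowledge of arm; the risk is probably modest and is cheap to close

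*Protocol article*

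**What the plan says.** All references are to the protocol article.

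- **Randomization and allocation:** "This RCT is not blinded". Participants can infer their arm from what they receive, and the primary investigator "will be aware of randomization assignment because intervention materials will be delivered through WeChat". Delivery is the only reason given for the investigator's knowledge.
- **Study setting and recruitment:** WeChat "will be used to deliver messages and collect confirmatory photos of hepatitis test reports from participants".
- **Outcomes:** a man counts only if he has "submitted a photo to researchers through WeChat or the online follow-up survey that clearly displays tester age, tester sex, test date", together with both serology results. That makes five items: age, sex, date, HBsAg and anti-HCV IgG. The date must fall within 28 days of enrolment. The recipients are called researchers and are not further identified.
- **Data collection and measures:** there is a second route: "Test report photos can also be uploaded along with the follow-up survey". On identifiers: "Mobile phone numbers and WeChat accounts will be used to link information extracted from test report photos to baseline and follow-up survey responses".
- **Confidentiality:** men are told to cover their name and other identifying details on the report.
- **Discussion:** photo confirmation is presented as the trial's advantage over self-reported testing.

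The article does not say who accepts or rejects a photo, whether that person can see the arm, or how a partly legible photo is handled.

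**The concern.** Delivery of images and videos cannot be masked from the person who sends them. Reading a laboratory report can be, and the reason given for the lack of blinding does not extend to it.

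The primary outcome is an acceptance decision on a phone photo. Reports come from any facility the man chooses, so layouts will vary, and parts of each report will be covered on instruction. Most photos will be plainly acceptable or plainly not. For the remainder, legibility is a judgement. If it is made by someone who knows the arm, marginal photos could be treated differently in the two arms. Documentary proof guards against misreporting by participants but not against this. The component outcomes (confirmed HBV and confirmed HCV test uptake) rest on the same reading.

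**Working it through.** **1. What follows from the text, and what does not**

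| Step | Status |
|---|---|
| Trial open; primary investigator knows the arm | Stated (Randomization and allocation) |
| WeChat both delivers materials and collects photos | Stated (Study setting and recruitment) |
| Photos may instead come with the follow-up survey | Stated (Outcomes; Data collection and measures) |
| Photo data linked to the man by phone number and WeChat account | Stated (Data collection and measures) |
| Primary outcome requires five legible items | Stated (Outcomes) |
| The person who delivers materials also reads the photos | Not stated |
| Photos return in the same chat as the materials | Not stated |
| Men are asked to resend unclear photos | Not stated |

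The stated steps leave room for an arm-aware reading but do not show that one will happen.

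**2. The plan's own figures**

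Sample size assumes a "testing response of 8.5% among intervention participants, 3.0% among control participants", two-sided 5%, an exact test and 10% not evaluable. Full enumeration of Fisher's exact test gives 80.0% power at 303 per arm. Then 606 / 0.9 = 673.3, rounded up to 674, as stated. At 700 × 0.9 = 630 evaluable, power is 81.8%, matching the stated 82%. The sample size is not in question here.

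**3. How many photos carry the result**

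The intention-to-treat analysis counts non-responders as not tested, so the denominator is n = 350 per arm.

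- Expected accepted photos: 350 × 0.085 = 29.75 and 350 × 0.03 = 10.5, about 40 in total.
- One photo decided differently moves the difference by 1/350 = 0.29 percentage points, or 0.286 / 5.5 = 5.2% of the planned difference.

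Wald interval: d ± 1.96 × √[p₁(1−p₁)/n + p₂(1−p₂)/n]

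| Accepted (intervention v control) | Difference | 95% CI |
|---|---|---|
| 30 v 10 | 5.7 points | 2.3 to 9.1 |
| 21 v 10 | 3.1 points | 0.1 to 6.2 |
| 20 v 10 | 2.9 points | −0.1 to 5.9 |

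Near the planned result a few photos do not change the conclusion. Near the boundary a single photo does.

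**4. False declaration of superiority when the arms do not differ**

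Sum Bin(a; 350, p₁) × Bin(b; 350, p₂) over all pairs (a, b) whose lower Wald limit exceeds zero. True testing is set at 3% in both arms, so 10.5 photos are expected per arm.

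| Extra accepted intervention photos (assumed) | Share of 10.5 | p₁ | P(declare superior) |
|---|---|---|---|
| 0 | 0% | 0.0300 | 2.5% |
| 1 | 9.5% | 0.0329 | about 4.1% |
| 3.5 | 33% | 0.0400 | about 10.6% |

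An alternative assumption is that every intervention photo is accepted and a fixed share of control photos is refused:

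| True rate, both arms | Control acceptance 90% | Control acceptance 80% |
|---|---|---|
| 3.0% | 4.3% | 7.1% |
| 5.75% | 5.2% | 10.1% |
| 8.5% | 6.0% | 13.2% |

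These use the Wald rule throughout. The Data analysis section allows an exact interval if proportions are too low for it, which would change the figures somewhat.

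**The case against.** **This is an absence in a journal article.** The reader's identity and the handling of files could stand in a full protocol that is not shown. That is fair, and if masked reading is written there, one sentence in the article closes the point. But the article does take up blinding, and it explains the investigator's knowledge by delivery alone, which is no reason to leave photo reading unmasked. Masked reading must also be settled before photos are judged; an analysis plan cannot restore it afterwards.

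**The criteria are fixed and mostly objective.** Printed age, sex, date and two named results are largely present-or-absent checks. This stands, and it is why the bias is probably modest.

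**Stronger readings that the documents do not support.** A reader might infer that:

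- the primary investigator reads the photos, whereas the article says only researchers;
- photos come back in the chat where the materials are visible, whereas the article names an app, not a thread, and the survey upload lies outside the chat;
- men in one arm will be asked to resend, although no resend procedure is described;
- the claim of documentary verification is false, although it remains a real gain over self-report even with an unmasked reader;
- false-positive risk is in fact near 11%. That figure needs 3.5 extra photos on 10.5 expected from leniency alone. It is a severe case, not an expectation.

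**Conclusion.** The concern holds as a risk left open, not as a demonstrated bias. The plan makes acceptance of a photo the primary outcome, states that the trial is open, and does not keep the acceptance decision apart from knowledge of arm.

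Its size cannot be fixed from the documents, because the share of borderline photos is unknown. The illustrations also assume that all differential decisions favour the intervention. On those terms, and with equal true rates of 3%, the milder cases (one extra photo, or 90% against 100% acceptance) give a false-superiority chance of a little over 4% in place of 2.5%. This is a worthwhile low-cost improvement. It does not invalidate the endpoint.

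**What to change.** In Randomization and allocation and in Outcomes, state that:

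1. Every submitted report photo, from WeChat and from the follow-up survey, is saved under a code with sender, chat and arm removed.
2. Acceptance against the existing Outcomes criteria is decided on the coded files, in mixed order and before linkage to arm. Where possible the reader is an existing team member who did not deliver materials. The same person reading coded files is weaker masking, since photos already seen may be recognised.
3. Clearer photos are handled in one of two ways. Either all men in both arms get one standard photo instruction and no individual resend requests are made, or a resend is triggered only by the coded reading. The second option requires reading in batches during collection, because a reading made after collection closes cannot prompt a resend.
4. Rejected photos are reported by arm, so that any imbalance is visible.

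**Cost.** Somewhat more than 40 files must be coded, because rejected photos, single-virus reports and separate HBV and HCV reports add to the roughly 40 expected acceptances. Reimbursement must be handled separately from the coded reading. No extra staff are needed, and no change is made to sample size, endpoint definition, intervention or analysis.

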### Intervention and control

Men randomly assigned to the intervention arm will receive a two-part crowdsourced intervention. The multimedia component of the intervention will deliver two images and two one-minute videos to men through WeChat. One image or video will be delivered every other day after enrolment, for a total of 8 days. Intervention images and videos were developed through a public nationwide crowdsourcing contest conducted in China in 2017.

A steering committee consisting of representatives from 13 national and international organizations was formed to organize a contest to solicit multimedia materials that promote HBV and HCV testing and reduce stigma toward people living with viral hepatitis. An initial public call for images and one-minute videos was promoted through social media and partner organizations. In total, 168 submissions were collected between February and May 2017. All submissions were first evaluated for eligibility and were then reviewed by a judging panel composed of steering committee members. Judges evaluated submissions on a 10-point scale based on each submission’s innovation and creativity, capacity to promote hepatitis testing, and potential to increase social media responsiveness. The twelve highest scoring entries were selected as semi-finalists and provided with feedback for improvement. Semi-finalists then had the opportunity to resubmit their images or videos. Eight submissions (four images and four videos) were selected as contest finalists, with five receiving third place, two receiving second place, and one receiving first place.

To select the finalist entries most appropriate for MSM in China, an online poll was conducted in August 2017. The poll was promoted through local MSM organizations and their social media accounts. Thirty MSM were asked to rank the four finalist videos, and a separate 30 MSM were asked to rank the four finalist images. The two top-ranked images and videos from this poll were selected as materials to be used in the intervention arm of the RCT (intervention images are available in Supplementary Materials as Additional file 1 and Additional file 2).

Because the strength of crowdsourcing includes not only the inflow of creative solutions and new ideas, but also facilitation of active participation and community engagement, the intervention will also include a participatory component. After viewing each image and video, men will be invited to participate in a crowdsourcing contest. Men can submit 50- to 200-word suggestions for how to improve the intervention images and videos to convince more MSM in China to receive hepatitis testing. A contest steering committee composed of hepatitis experts and community representatives will judge each submission on a 10-point scale, and the highest-scoring eight submissions will receive prizes.

Men randomly assigned to control will not view any images or videos and will not be invited to submit ideas for improving hepatitis testing promotional materials. All participants will be informed at enrolment that costs of HBV and HCV testing during the four-week study period can be reimbursed. Because this study is designed as a pragmatic trial with results that will be generalizable to multiple settings, men will be allowed to receive hepatitis testing at any hospital, clinic, or healthcare centre of their choosing.

### Outcomes

HBsAg and anti-HCV IgG test uptake confirmed by test report photo at 4 weeks post-enrolment is the primary outcome of this study. This dichotomous outcome has two component endpoints (HBsAg test uptake and anti-HCV IgG test uptake) that constitute a single composite endpoint. Selection of HBsAg and anti-HCV IgG as serological assays is based on WHO testing guidelines [13]. A participant will only be counted as having the primary outcome if he has submitted a photo to researchers through WeChat or the online follow-up survey that clearly displays tester age, tester sex, test date, and HBsAg and anti-HCV IgG results. If submitted HBV test report photos also include anti-HBs and anti-HBc serological assays, these results will be recorded. Test date must fall within the four-week period (28 days) after enrolment for test uptake to be confirmed.

Confirmed HBsAg and anti-HCV IgG test uptake as independent component endpoints are secondary outcomes. Secondary outcomes also include the following self-reported items on the follow-up survey: HBsAg test uptake, anti-HCV IgG test uptake, HIV test uptake, chlamydia test uptake, gonorrhoea test uptake, syphilis test uptake, visit with specialist physician after HBV or HCV testing, and change in stigma toward people living with HBV during the four-week study period. Self-reported HBV vaccination uptake among all participants and those with confirmed susceptibility to HBV infection (negative anti-HBs and negative HBsAg by test report photo) are also secondary outcomes. Definitions for all study outcomes are provided in Table 1.

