### Objectives

Specific aim 1: To compare confirmed HBV and HCV test uptake as a composite endpoint between MSM randomly assigned to a crowdsourced intervention and MSM randomly assigned to control.

Hypothesis 1: MSM assigned to the crowdsourced intervention will have a higher rate of HBV and HCV test uptake compared to MSM in the control arm.

Specific aim 2: To compare change in stigma toward people living with HBV between MSM randomly assigned to a crowdsourced intervention and MSM randomly assigned to control.

Hypothesis 2: MSM assigned to the crowdsourced intervention will have greater reduction in stigma toward people living with HBV compared to MSM in the control arm.

Specific aim 3: To compare self-reported linkage to clinical visits about hepatitis, HBV vaccination, and HIV/STI testing services between MSM randomly assigned to a crowdsourced intervention and MSM randomly assigned to control.

Hypothesis 3: MSM assigned to the crowdsourced intervention will have improved linkage to clinical visits about hepatitis, HBV vaccination, and HIV/STI testing services compared to MSM in the control arm.

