HBV vaccination uptake among men with confirmed susceptibility to HBV infection	Defined as men with negative HBsAg and negative anti-HBs results confirmed through electronic submission of a test report photo showing serology results, who had receipt of at least one dose of the HBV vaccine within four weeks of enrolment, self-reported in follow-up survey
HIV test uptake	Defined as men who had HIV test uptake within four weeks of enrolment, self-reported in follow-up survey
Chlamydia test uptake	Defined as men who had chlamydia test uptake within four weeks of enrolment, self-reported in follow-up survey
Gonorrhoea test uptake	Defined as men who had gonorrhoea test uptake within four weeks of enrolment, self-reported in follow-up survey
Syphilis test uptake	Defined as men who had syphilis test uptake within four weeks of enrolment, self-reported in follow-up survey
Change in stigma toward people living with HBV	Continuous variable, defined as difference between Toronto Chinese HBV Stigma Scale score assessed at follow-up and baseline. Stigma toward people living with HBV will be measured at baseline and follow-up using 20 survey items that are each on a five point Likert scale. The 20 items were originally developed as the Toronto Chinese HBV Stigma Scale (potential range of 20–100), which has been previously validated and correlated to HBV testing behaviours among Chinese populations [39]. Decreased stigma toward people living with HBV will be defined as a mean composite score that is less at follow-up compared to baseline.
Visit with a physician after hepatitis test uptake	Defined as men who had HBV and/or HCV test uptake and saw a physician to discuss hepatitis test results within four weeks of enrolment, self-reported in follow-up survey

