#### Secondary analyses

The intervention and control arms will also be compared for differences in proportions of men achieving secondary outcomes, including confirmed HBsAg test uptake (independent of anti-HCV IgG test uptake), confirmed anti-HCV IgG test uptake (independent of HBsAg test uptake), self-reported HBsAg and anti-HCV IgG test uptake, HBV vaccination, and HIV and STI test uptake during the four-week study period. The analysis approach will be as described for the primary outcome. Change in stigma toward people living with HBV from baseline to week four will be calculated and compared between the intervention and control arms using a Wilcoxon ranksum test.

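### HBV vaccination among confirmed-susceptible men is defined in a group formed by post-randomisation testing, so a between-arm comparison there is not protected by randomisation; the denominator needs to be fixed

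*Protocol article*

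**What the plan says.** The Outcomes section lists "Self-reported HBV vaccination uptake among all participants and those with confirmed susceptibility to HBV infection", where susceptibility means "negative anti-HBs and negative HBsAg by test report photo) are also secondary outcomes". The two populations are set side by side as separate outcomes, and the label in Table 1 likewise restricts this one to susceptible men.

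The definition beside that label (Table 1, under Trial design and timeline) runs differently. It begins "Defined as men with negative HBsAg and negative anti-HBs results confirmed through electronic submission of a test report photo showing serology results" and goes on to require at least one vaccine dose within four weeks, self-reported at follow-up. It names no denominator.

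Four other statements bear on who can enter the group:
- Eligibility criteria: "Men who report past HBV vaccination, HBV testing, or HCV testing will be excluded". Men who are uncertain about these remain eligible.
- Outcomes: "Test date must fall within the four-week period (28 days) after enrolment for test uptake to be confirmed".
- Outcomes: "If submitted HBV test report photos also include anti-HBs and anti-HBc serological assays, these results will be recorded".
- Objectives, the first of the three hypotheses: "MSM assigned to the crowdsourced intervention will have a higher rate of HBV and HCV test uptake compared to MSM in the control arm".

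The Secondary analyses section compares the arms on proportions achieving the secondary outcomes. It names HBV vaccination in a list introduced as non-exhaustive and adds: "The analysis approach will be as described for the primary outcome". The primary approach is an unadjusted difference in proportions with a confidence interval and a superiority rule.

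**The concern.** A randomised comparison holds for groups defined before randomisation, or by something treatment cannot alter. Here the group is defined by testing and sending a photo. Confirmed HBV testing is itself a secondary outcome and one of the two components of the primary outcome, and the trial expects treatment to change it. If the intervention works, its susceptible group will contain men who would not have tested under control. Those men may be more or less inclined to be vaccinated than men who test unprompted.

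A difference between arms in this group then mixes two things: any effect on vaccination, and the change in who was tested. A useful intervention could look harmful, or a benefit on vaccination could be claimed that only reflects who was drawn in.

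**Working it through.** **Planning figures.** The Sample size section assumes 8.5% against 3.0%, two-sided 5%, 10% not evaluable, and an exact test, giving 674 men for 80% power. This reproduces. Full enumeration of the two-sided Fisher test gives power 0.8003 at 303 per arm, and 606 / 0.90 = 673.3, rounded up to 674. At 700 × 0.90 = 630 evaluable (315 per arm) the power is 0.818, matching the stated 82%. The sample size is not in dispute; its rates are used below.

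**Size of the group.** These rates are for the composite of both tests. No HBV-only rate is given, so they serve as a proxy.
- Intervention testers: 350 × 0.085 = 29.75
- Control testers: 350 × 0.030 = 10.5

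The documents give no share of testers confirmed susceptible. Assumed shares of 30%, 50% and 70% give about 9 against 3, 15 against 5, and 21 against 7 men.

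**Overlap between the arms.** Assume that every man who would test under control would also test under intervention. Always-testers are then 3.0% of each arm and induced testers 8.5% − 3.0% = 5.5% of the intervention arm. The share of intervention testers without a control counterpart is 5.5 / 8.5 = 65%.

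**Effect on the comparison.** Let *a* be the vaccination proportion in susceptible always-testers (the same in both arms, so the intervention does not change their vaccination) and *b* that in susceptible induced testers. Let *s* be the susceptible share, assumed equal in both types.
- Subgroup, intervention: (0.030*a* + 0.055*b*) / 0.085
- Subgroup, control: *a*
- All randomised, intervention: *s*(0.030*a* + 0.055*b*)
- All randomised, control: *s* × 0.030*a*

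The share *s* cancels from the subgroup proportions. The values of *a* and *b* are assumptions, shown as a range.

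| *a* | *b* | Subgroup: intervention vs control | Difference (points) | All randomised, each × *s* |
|---|---|---|---|---|
| 40% | 40% | 40.0% vs 40.0% | 0.0 | 3.40% vs 1.20% |
| 40% | 20% | 27.1% vs 40.0% | −12.9 | 2.30% vs 1.20% |
| 40% | 10% | 20.6% vs 40.0% | −19.4 | 1.75% vs 1.20% |
| 30% | 10% | 17.1% vs 30.0% | −12.9 | 1.45% vs 0.90% |
| 20% | 30% | 26.5% vs 20.0% | +6.5 | 2.25% vs 0.60% |
| 10% | 40% | 29.4% vs 10.0% | +19.4 | 2.50% vs 0.30% |

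Third row worked through: (0.030 × 0.40 + 0.055 × 0.10) / 0.085 = 0.0175 / 0.085 = 20.6%, against 40.0% in control. Over all randomised men the same inputs give 1.75% against 1.20%, each times *s*.

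In all six rows the all-randomised proportion is higher with intervention, while the subgroup contrast takes either sign or none.

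**The case against.** The strongest reply is that the protocol does not settle on the biased analysis. Table 1 can be read as a joint event: susceptible by photo and vaccinated. The Outcomes section refers to Table 1 for definitions, the Secondary analyses section speaks of men achieving outcomes, and the Missing data plan counts men lost to follow-up as not having achieved them. All of this fits a denominator of all randomised men. The Secondary analyses section also names only HBV vaccination, not the susceptible group. This stands in part. A reader might infer that the protocol expressly orders a superiority test in this group, and it does not. But the Table 1 label and the contrast with all participants in the Outcomes section point to the subgroup as denominator, so the text conflicts with itself.

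Other stronger readings are tempting and not supported:
- *The result will go against the intervention.* The documents give no vaccination propensities, so the direction is unknown.
- *The Wald interval is the fault.* The Primary analysis section provides an exact interval when the Wald assumptions fail. Its trigger is worded around low testing proportions, but in any case the choice of interval does not cure selection.
- *The physician-visit outcome has the same defect.* Table 1 words it as a joint event (tested and saw a physician), with no restriction to testers.
- *Whether anti-HBs appears on a report is chance.* It need not appear, but it belongs to the standard panel on which reimbursement is based, so many reports may carry it. Selection through testing and sending a photo remains.

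It is also fair that the consequence is limited: vaccination among all participants is a separate secondary outcome and keeps the randomised comparison.

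**Conclusion.** The point holds conditionally. If the primary-outcome method is applied among confirmed-susceptible men, the contrast is not a randomised comparison. It can show nothing, a reversal (−19.4 points in the 40%/10% case) or a spurious benefit (+19.4 points in the 10%/40% case), with no effect on vaccination in men who would test anyway. The 65% without a counterpart rests on the planning rates as a proxy for HBV testing and on control-type testers also testing under intervention. The sizes of the differences rest further on the assumed propensities and an equal susceptible share.

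The objection is to a population that the protocol itself states, so it is not a matter of detail left to an analysis plan. It concerns one secondary outcome and should be corrected. The primary outcome and vaccination among all participants are unaffected.

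**What to change.** In Table 1, Outcomes and Secondary analyses, define the outcome as a single event: tested, confirmed susceptible by report photo, and vaccinated within four weeks. State all randomised men (350 per arm planned) as the denominator, and relabel the outcome accordingly. This event combines testing with vaccination, so it should be interpreted as the effect of the whole intervention on reaching that endpoint.

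Report the proportion vaccinated among confirmed-susceptible men by arm, descriptively, with numerators and denominators and without a test or superiority statement.

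The cost is wording in three places. No new data, participants or assessments are needed, and the physician-visit outcome needs no change.
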